## Abstract

**Background:**

Spirituality is vital to holistic patient care and should be proactively addressed by healthcare providers as unmet spiritual needs are a major source of suffering for patients living with chronic illnesses. However, spiritual concerns are seldom referenced by clinicians during disease-related treatment discussions, particularly for minority and under-resourced patients. This paper outlines a protocol for administering and evaluating a culturally-responsive spiritual care intervention conducted with chronically ill African Americans receiving care at a community safety net health service.

**Methods:**

A total of 60 African American patients who have chronic conditions and are aged 50 or older will be recruited for this study and randomly assigned to either the intervention (spiritual care program delivered by a board-certified chaplain) or the control group. All participants will complete a baseline interview that encompasses demographic information, religiosity, spiritual well-being, quality of life, and perception of care. Follow-up surveys will be conducted 12 weeks post-baseline, and participants assigned to the intervention group will also undergo a semi-structured acceptability and feasibility interview. Effect size measures and bivariate tests will be used to compare pre- and post-test outcomes while the interviews will be analyzed using constant comparative and thematic analysis.

**Discussion:**

Study findings will assess the feasibility and effectiveness of a culturally-responsive spiritual care intervention for under-resourced African American patients with chronic illnesses. Furthermore, the provision of spiritual care may help patients clarify their healthcare values and decision making priorities.

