Recognizing the importance of these concerns, the 4^th^ Edition of the Clinical Practice Guidelines for Quality Palliative Care identifies spiritual, religious, and existential aspects of care as one of the key domains integral to delivering high-quality PC [18]. Spiritual care (SC) aims to recognize and respond to the needs of patients as they cope with trauma, illness, or grief [19]. Addressing spiritual needs is particularly important for addressing the structural inequalities related to PC and EOL care. AAs, for example, frequently experience poor communication regarding care options and goals of care [20], highlighting the necessity for culturally-responsive conversations and education regarding EOL decision making [6]. Ongoing spiritual support could help patients and family members be more accepting of PC and EOL care options [8].

This paper describes the study protocol for a culturally adapted SC intervention designed to support older AAs with heart failure (HF), chronic kidney disease (CKD), or chronic obstructive pulmonary disease (COPD) who are receiving care at a community safety net health service. This study aims to assess the acceptability, feasibility, and preliminary impact of the intervention on spiritual well-being, quality of life, and perception of care. HF, CKD, and COPD represent a substantial share of the chronic disease burden among AAs [21]; yet AAs living with these conditions remain underrepresented in clinical trials [22–24]. To address this gap, our study focuses on this population to generate data that can inform person-centered, culturally-responsive care. By centering the lived experiences and needs of older AAs with chronic illness, we aim to support the development of evidence-based practices that reduce disparities and improve outcomes in a group often overlooked in clinical research.

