### Study procedures

60 participants will complete pre-test measures at baseline, after which half will be randomized to receive usual care, in addition to post-test measures following the completion of the intervention. Questionnaires will include demographic information, spiritual well-being (Functional Assessment of Chronic Illness Therapy – Spiritual Well-Being 12 Item Scale) [31], religiosity (Duke University Religion Index) [32], religious coping (Scale of Religious and Spiritual Coping) [33], quality of life (Functional Assessment of Cancer Therapy- General) [34], perception of care (Older Patient Assessment of Chronic Illness Care) [35], treatment burden (Treatment Burden Questionnaire) [36], distress (Distress Thermometer) [37], hope (Trait Hope Scale, State Hope Scale) [38,39], anxiety and depression (Hospital Anxiety and Depression Scale) [40]. For the purposes of this study, feasibility will serve as the primary outcome, with the others as secondary to explore preliminary impacts to guide subsequent larger studies.

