### Acceptability and feasibility

Semi-structured acceptability interviews will be conducted with patients in the intervention arm two weeks after completing the SCAI program with the SC specialist. These interviews, conducted by study staff, will explore patients’ perceptions of the program, its impact, and any suggestions for improvements.

We aim for a 75% completion rate of study activities, defined as the proportion of enrolled participants who complete all components of the study protocol. This benchmark is consistent with retention rates of similar longitudinal clinical studies and reflects a realistic threshold to ensure the acceptability, feasibility, and relevance of our culturally tailored intervention to the target population [41–43].

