### Data analysis

#### Quantitative analysis.

Data from pre- and post-intervention questionnaires will be analyzed with SPSS; measures of effect size and bivariate tests of associations will be conducted to compare pre- and post-test measures. Due to the small sample size, broad patterns of responses will be examined.

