### Future directions

Future research should focus on efficacy testing to determine the intervention’s effectiveness in improving clinical outcomes and its ability to produce sustained effects over longer periods of time. Studies should also examine the durability of intervention effects in community and natural care environments in response to health status changes. Efficacy testing in future studies may also assess the potential for implementation scaling in acute, short-term, and long-term care settings. In addition, future work should explore setting-specific adaptations and the potential development of structured protocols that may standardize SC delivery, guide provider training, and ensure fidelity, while allowing flexibility to accommodate diverse cultural and faith values so that enhancements to traditional care remain both responsive and relevant.

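### The abstract promises an assessment of effectiveness that the main text leaves to later research, and the stated pre/post tests do not compare the randomized arms

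*Protocol article*

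**What the plan says.** The closing paragraph of the abstract (Discussion) reads "Study findings will assess the feasibility and effectiveness of a culturally-responsive spiritual care intervention".

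The main text describes the purpose differently:

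- Introduction: "This study aims to assess the acceptability, feasibility, and preliminary impact of the intervention", with spiritual well-being, quality of life and perception of care as the targets.
- Study procedures: "feasibility will serve as the primary outcome, with the others as secondary to explore preliminary impacts to guide subsequent larger studies".
- Discussion, Summary and significance: the study is a pilot that explores acceptability and feasibility.
- Future directions: "Future research should focus on efficacy testing to determine" whether the intervention is effective on clinical outcomes.

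Study procedures lists ten instruments besides demographics: FACIT-SP-12, DUREL, RCOPE, FACT-G, O-PACIC, TBQ, Distress Thermometer, Trait Hope Scale, State Hope Scale and HADS. For these, Quantitative analysis says that effect sizes and "bivariate tests of associations will be conducted" to compare pre-test with post-test measures. The abstract's Methods says the same. Quantitative analysis adds that, because the sample is small, only broad patterns will be examined. No significance level, power or precision target is given.

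**The concern.** Two things are wrong, and each makes the other worse.

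First, the abstract claims for this trial the very question that Future directions hands to later studies. Many readers will see only the abstract.

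Second, the only quantitative comparison described is before against after. In a randomized trial the effect of the intervention is the difference between arms. A change within one arm also contains the course of the illness, usual care, and the experience of being in a study and answering the same questions twice. A significant change in the intervention arm beside a non-significant one in the control arm is not a test of the difference either. With ten instruments, one or more could move by chance, and the abstract's wording would let that be presented as effectiveness.

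**Working it through.** **Inputs**

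- Total sample: "A total of 60 African American patients who have chronic conditions and are aged 50 or older will be recruited" (abstract, Methods).
- Allocation: "after which half will be randomized to receive usual care" (Study procedures), so 30 per arm.
- Completion: "We aim for a 75% completion rate of study activities" (Acceptability and feasibility). 0.75 × 60 = 45, or 22.5 per arm. This is a proxy for the number analysed, because a patient may answer the 12-week questionnaire and miss another study activity.
- Number of instruments: 10 (Study procedures).
- Assumed, because not stated: two-sided 5% level; outcomes in SD units; correlation r between baseline and 12 weeks of 0.5 to 0.7.

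The plan gives no statistical basis for 60, so there is no figure to reproduce.

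**Purpose, side by side**

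| Place | Claim for this trial |
|---|---|
| Abstract, Discussion | feasibility and effectiveness |
| Introduction | acceptability, feasibility, preliminary impact |
| Study procedures | feasibility primary, the rest exploratory |
| Summary and significance | acceptability and feasibility |
| Future directions | effectiveness left to later research |

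Four places agree and the abstract's Discussion stands alone.

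**Chance findings.** For k independent tests with no true effect, P(at least one significant) = 1 − 0.95^k.

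- k = 10: 1 − 0.95^10 = 0.40.
- k = 3 (only the impact targets named in the Introduction): 1 − 0.95^3 = 0.14.

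The scales measure related things, so the true figures are lower.

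**Precision of a between-arm difference, unadjusted.** Half-width of the 95% interval = t × √(2/n).

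- n = 30 per arm, 58 df: 2.002 × 0.258 = 0.52 SD.
- n = 22.5 per arm, 43 df: 2.017 × 0.298 = 0.60 SD.

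An observed difference of 0.3 SD would then have an interval of about 0.3 ± 0.52 = −0.22 to 0.82, or 0.3 ± 0.60 = −0.30 to 0.90.

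**With baseline adjustment.** Multiply by √(1 − r²), which is 0.866 at r = 0.5 and 0.714 at r = 0.7.

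- 60 analysed: 0.517 × 0.866 = 0.45 SD, down to 0.517 × 0.714 = 0.37 SD.
- 45 analysed: 0.601 × 0.866 = 0.52 SD, down to 0.601 × 0.714 = 0.43 SD.

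**Power, unadjusted, normal approximation.** Φ(d/√(2/n) − 1.96).

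| True difference | 30 per arm | 22.5 per arm |
|---|---|---|
| 0.3 SD | 21% | 17% |
| 0.5 SD | 49% | 39% |
| 0.8 SD | 87% | 77% |

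**The case against.** The strongest reply is that the body of the article is already cautious. It labels the scales exploratory, lists effect sizes before tests, states no significance level, and limits itself to broad patterns because of the sample size. This stands: it would be wrong to say that nothing restrains the claims. It does not remove the conflict, because the abstract still promises what the body disclaims.

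A second reply is that a condensed article may leave the between-arm model to a statistical analysis plan that is not shown. That is fair for details such as covariates, and the absence of a named lead scale is no fault here for the same reason. But the article does not stay silent on the comparison. Twice it states one, and it is pre against post.

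A reader might go on to infer three stronger things, which the documents do not support:

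- *That 60 patients are too few to estimate any scale usefully.* No precision target exists to fail, the sample serves a feasibility aim, a difference of 0.8 SD would have 77% to 87% power, and the data can still inform SDs, correlations and retention.
- *That the false-positive risk is well above 40%.* This needs a count of subscale tests that the plan does not fix. Splitting DUREL into three, FACT-G into four and HADS into two gives 10 + 2 + 3 + 1 = 16 tests and 1 − 0.95^16 = 56%, but nothing says each will be tested.
- *That the next trial will be undersized.* The article says only that the results will guide larger studies, not that the observed effect will set their size.

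**Conclusion.** The point holds in two parts. The contradiction over effectiveness is textual and rests on no assumption. The stated pre/post comparison does not use the randomization, so by itself it cannot support a statement about the effect of the intervention.

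The figures show why the wording matters. They do not show that the sample size is wrong. Up to a 40% chance of at least one significant result among ten tests assumes independence and a 5% level. Intervals of ±0.52 SD (60 analysed) to ±0.60 SD (45 analysed) are for an unadjusted comparison. Small to moderate differences could not be told from zero reliably; large ones probably could. The primary feasibility outcome is unaffected.

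**What to change.** 1. In the abstract's Discussion, replace effectiveness with preliminary impact, to match the Introduction and Study procedures.
2. In the abstract's Methods and under Quantitative analysis, state that each scale will be reported as the difference between arms at 12 weeks, adjusted for its baseline value, with a 95% confidence interval. The baseline interview precedes randomization, so the baseline score is a valid covariate. Pre-to-post change within each arm can stay as description.
3. Add that these estimates are exploratory and will not be read as evidence of effectiveness, whether or not an interval excludes zero.

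The cost is wording and a standard model on data already being collected; the sample size does not change. The article reports 21 patients randomized as of October 2025 and analysis from July 2026, so on that timetable the change can be recorded before analysis. The small downside is that the sponsor gives up presenting a significant secondary result as effectiveness.

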## Introduction

Chronic diseases are persistent health conditions that require ongoing medical attention and may interfere with daily functioning. Such illnesses are also the leading cause of disease, disability, and death in the United States (US), and certain populations are at greater risk of developing chronic diseases [1]. African American (AA) Medicare beneficiaries have higher prevalence rates of chronic conditions such as hypertension, diabetes, and stroke in comparison to their White counterparts, with over a third of AA beneficiaries reporting fair or poor health [2].

Palliative care (PC) can mitigate the burden of chronic illness by enhancing quality of life and addressing the emotional, physical, and spiritual distress experienced by patients and their families. Although it can be introduced at any point during the course of a serious illness and continue throughout the disease progression to end-of-life (EOL) [3], PC and EOL care are underutilized among AA patients despite their high burden of chronic disease [4,5]. Barriers that contribute to these disparities in usage include a lack of information and poor perceptions of EOL care, incongruence with cultural values, and mistrust of the medical system [6–10]. In addition, this underuse may also arise from the absence of culturally-responsive communication that would prompt AA patients with chronic illnesses to identify their values and priorities [6,11].

For many individuals, spirituality is an essential component of the human experience and must be proactively addressed by healthcare providers to deliver care that honors the whole person [12]. For patients with life-limiting illnesses, spirituality can offer vital support in coping with their condition with many considering it fundamental to the healing process [12,13]; some individuals may make critical healthcare decisions on the basis of their religious or spiritual beliefs [14]. Among older AA adults with chronic conditions, prayer and faith have been expressed as important coping mechanisms [15]. Yet, spiritual considerations are seldom referenced by clinicians during disease-related treatment discussions [16], especially for patients from minority and under-resourced populations [17].

Recognizing the importance of these concerns, the 4^th^ Edition of the Clinical Practice Guidelines for Quality Palliative Care identifies spiritual, religious, and existential aspects of care as one of the key domains integral to delivering high-quality PC [18]. Spiritual care (SC) aims to recognize and respond to the needs of patients as they cope with trauma, illness, or grief [19]. Addressing spiritual needs is particularly important for addressing the structural inequalities related to PC and EOL care. AAs, for example, frequently experience poor communication regarding care options and goals of care [20], highlighting the necessity for culturally-responsive conversations and education regarding EOL decision making [6]. Ongoing spiritual support could help patients and family members be more accepting of PC and EOL care options [8].

This paper describes the study protocol for a culturally adapted SC intervention designed to support older AAs with heart failure (HF), chronic kidney disease (CKD), or chronic obstructive pulmonary disease (COPD) who are receiving care at a community safety net health service. This study aims to assess the acceptability, feasibility, and preliminary impact of the intervention on spiritual well-being, quality of life, and perception of care. HF, CKD, and COPD represent a substantial share of the chronic disease burden among AAs [21]; yet AAs living with these conditions remain underrepresented in clinical trials [22–24]. To address this gap, our study focuses on this population to generate data that can inform person-centered, culturally-responsive care. By centering the lived experiences and needs of older AAs with chronic illness, we aim to support the development of evidence-based practices that reduce disparities and improve outcomes in a group often overlooked in clinical research.

## Methods

### Theoretical model

The study is informed by the Biopsychosocial-Spiritual Model of Care (BSMC) which supports a holistic view of the patient and recognizes spirituality (i.e., an individual’s search for transcendent meaning) as a fundamental aspect of human well-being [25]. The model posits that spiritual well-being influences not only health behaviors but also how patients experience and cope with illness. Serious illness can disrupt spiritual connectedness, leading to distress that may affect relationships with the self, others, and the transcendent. SC interventions grounded in the BSMC aim to restore balance across biological, psychological, and spiritual domains—especially for chronically ill patients in under-resourced communities.

### Study design, setting, and sample

The study will use a randomized multi-method approach. Participants will be recruited from the cardiac, pulmonary, and renal clinics of Cooper Green Mercy Health Services Authority (CGMHSA), a publicly funded, safety net health system located in Jefferson County, Alabama.

Eligible participants will: (1) self-identify as AA, (2) be at least 50 or older, (3) speak English, (4) have a diagnosis of a least one of the following conditions based on chart review—HF, CKD, or COPD, 5) be cognitively able to participate in the SC intervention and complete study questionnaires, and 6) have reliable telephone access. Patients will be excluded if they: (1) have an Axis I psychiatric (e.g., schizophrenia, bipolar disorder) disorder, dementia, or active substance use disorder or (2) reside in a nursing home or assisted living facility.

### Recruitment procedures

Recruitment will utilize previously successful procedures [26] in which the eligibility criteria (outlined above) are applied as screening parameters to identify patients through an electronicmedical record (EMR) review of diagnostic codes; a comprehensive list of patients meeting those criteria was generated and securely transmitted to the Principal Investigator via an encrypted electronic file. Eligible participants will receive an opt-out letter and a flyer by mail, detailing the study’s purpose and procedures. The letter will inform recipients that they will be contacted in two weeks unless they call the study phone number to opt out. After the two-week opt-out window, study staff will contact individuals who have not declined participation to provide details about the study. During this call, study staff will assess the individual’s interest in participating in the SC program. Participants expressing interest will be consented through Institutional Review Board (IRB)-approved verbal consent. Patients will receive $25 for each data collection activity they complete—baseline questionnaire, 12-week post-baseline follow-up questionnaire, and semi-structured interview (intervention group only)—for a maximum of $75 for completion of all study activities for intervention group participants and $50 for usual care group participants.

### Randomization

Following the completion of the baseline interview, participants will be randomly assigned to receive either usual care from CGMHSA or the culturally-responsive SC intervention administered by a trained SC specialist (i.e., a board-certified chaplain) using stratified block randomization by sex and clinic type in REDCap. Since the intervention is administered as a feasibility pilot, the Principal Investigator and study staff will not be blinded. The participant flow is depicted in Fig 1.

**Fig 1 pone.0337436.g001:**
[figure not shown]
Flowchart of study procedures.

### Spiritual Care and Assessment Intervention (SCAI)

The SCAI is a chaplain-delivered SC intervention comprised of four core components: (1) proactive contact, (2) a semi-structured spiritual assessment, (3) individualized SC, and (4) documentation of interaction [27]. SCAI is structured around four dimensions: Meaning and Purpose, Relationships, Transcendence and Peace, and Self-worth and Identity [27]. Originally designed for family members of seriously ill patients, SCAI has demonstrated feasibility and acceptability among advanced-stage cancer outpatients [28] and improved the spiritual and psychological outcomes for surrogate decision makers in intensive care settings [29]. However, this intervention has not yet been evaluated for acceptability or feasibility among AA patients. Previous qualitative interviews with AA patients and clinicians suggested adaptations to increase cultural responsiveness, including reducing the intervention length from 90 down to 60 minutes and delivering it in person [30]. These modifications will be incorporated in the current pilot.

Patients assigned to receive the SCAI will be contacted by an SC specialist to schedule an in-person appointment that will take place in-clinic at the participant’s convenience. If the participant is unable to meet in person for any reason, the session will occur instead over Zoom. At the visit, the SC specialist will ask semi-structured questions pertaining to each of the SCAI’s dimensions to gauge the patient’s spiritual needs. During this assessment, patients may be asked about their sources of strength, their connections to other people, and any stress they may be experiencing [27]. The SC specialist will then tailor and administer the intervention according to their perception of the participant’s specific needs; potential interventions may include active listening, prayer, reading of sacred texts, or emotional support [27]. Patients will also receive one follow-up phone call after the initial visit. At this time, the participant and SC specialist may reflect on, revisit, or explore their previous discussions in greater depth.

To ensure intervention fidelity, all SC specialists are required to achieve at least 80% adherence to the SCAI protocol, as assessed through a structured fidelity checklist. The SC specialists will undergo a standardized four-hour training delivered by the original developers of the intervention and will participate in ongoing quarterly fidelity monitoring and booster training sessions conducted by certified SCAI interventionists throughout the recruitment and implementation period. These sessions will reinforce core components of the intervention, address implementation challenges, and promote consistency in delivery across sites and time points.

